### Statistical analysis

Patients with at least one post-randomisation observation will be included in the analysis. Missing data will be described using summary statistics. Data will be checked and cleaned blind to the actual treatment allocation. Data checking will be conducted throughout the study and prior to any analysis of the data.

Primary and key secondary endpoints for the comparisons of control to intervention and active control to intervention will be analysed using a Hochberg testing procedure, which allows for an investigation of all three endpoints whilst maintaining the overall type I error at 5% [32]. This approach has the advantage of not inflating the sample size while maintaining the type I error rate at 5%.

Significance will be declared for the comparison of usual care to intervention if and only if both primary outcomes, word retrieval and conversation, are significant at the 5% level, or if either comparison is significant at 2.5%. If and only if significance is declared for both primary outcomes, a similar comparison of attention control to intervention will be made. Significance will be declared for the comparison of attention control to intervention if and only if both word retrieval and conversation are significant at the 5% level, or if either comparison is significant at 2.5%.

If and only if significance is declared for the comparison of attention control to intervention for both comparisons will the key secondary outcome measure (patient perception of communication and related quality of life, measured using the COAST rating scale) be used in a further comparison of usual care to intervention. If and only if this comparison is significant at the 5% level will the intervention be compared to attention control based on the COAST questionnaire (see Figure 2).

**Figure 2 Fig2:**
[figure not shown]
**Statistical testing procedure.** COAST = Communication Outcomes After Stroke questionnaire.

Primary analysis will take an intention-to-treat approach (ITT) for all key measures, and further exploratory analysis of participants who complied with the intervention will be undertaken using the same statistical tests, according to the per protocol principle (PP). Only patients with post-randomisation observations will be included in the primary analysis at six months. A sensitivity analysis responses will be imputed as appropriate with details provided in the statistical analysis plan.

The mean difference in percentage improvement of words named correctly between the treatment and control groups, adjusted for baseline naming ability, will be analysed using an analysis of covariance (ANCOVA). Terms for treatment and baseline will be fitted into the model. Assumptions underlying the analyses will be assessed by inspection of residual plots. Homogeneity of variance will be assessed by plotting the studentised residuals against the predicted values from the model, whilst Normality will be assessed by use of Normal probability plots. If the assumptions for the analysis of variance are violated then appropriate transformations may be applied or alternative analyses may be performed. Similar analyses will be undertaken for the endpoints of functional conversation ability (measured by the activity scale of the Therapy Outcome Measures and patient-reported communication outcomes (the COAST questionnaire). The endpoints at nine and 12 months will be similarly analysed for exploratory purposes. Likewise an investigation of trends over time will be made.

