#### Other secondary

Evidence of treatment effect will be measured by repeating all outcome measures at nine and 12 months from baseline, in addition to the primary end point of 6 months. The nine-month time point is included as an interim measure as drop out from the study was found to increase over time in the pilot study [13].

Generalisation of treatment to retrieval of untreated words will be measured using the Naming Objects subtest from the Comprehensive Aphasia Test. Carer perception of communication effectiveness will be measured using the Carer COAST questionnaire [28]. Carer quality of life will be measured using the last five items of the Carer COAST questionnaire [28] and the CarerQol questionnaire [29]. Negative effects of treatment will be reported through diaries. Table 1 summarises the main measures and methods of data collection. Follow-up assessments will be conducted within one month of the target time point.

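### The analysis labelled ITT is an observed-case set, and the nine- and 12-month ANCOVAs discard six-month scores that one longitudinal model would use

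*Protocol article*

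**What the plan says.** The Statistical analysis section defines who is analysed twice. Its opening sentence gives a general set: "Patients with at least one post-randomisation observation will be included in the analysis". This set is not tied to a visit. After Figure 2 the section names the principle, "Primary analysis will take an intention-to-treat approach (ITT) for all key measures", and two sentences later restricts it: "Only patients with post-randomisation observations will be included in the primary analysis at six months".

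The model is an ANCOVA of the six-month outcome: "Terms for treatment and baseline will be fitted into the model". For the later visits, "The endpoints at nine and 12 months will be similarly analysed for exploratory purposes". Two further analyses are announced without a model: "A sensitivity analysis responses will be imputed as appropriate with details provided in the statistical analysis plan", and "Likewise an investigation of trends over time will be made".

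Four other places bear on this. Under Other secondary, the reason given for the nine-month visit is that "drop out from the study was found to increase over time in the pilot study". The Objectives section lists effects at 12 months among the primary objectives. The Blinding section says that participants know their allocation. The Randomisation section stratifies by centre and by naming severity.

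**The concern.** There are two separate problems.

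The first is definition. An intention-to-treat analysis normally takes in everyone randomised. The set described here leaves out anyone without follow-up, so it is an observed-case (or modified ITT) set. The two definitions also disagree about participants who miss six months and return later: the general set includes them, but a six-month ANCOVA has no outcome for them.

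The second is the method fixed for nine and 12 months. Each visit is analysed on whoever is still present, adjusted for baseline only. A participant who leaves after six months has contributed a six-month score that says a good deal about the missing 12-month value, and the stated model throws it away. Because participants are unblinded, those in usual care who are doing poorly could plausibly leave more readily than similar participants in the intervention arm. The 12-month contrast would then be distorted by information that the trial had in hand. What is at stake is the estimate of whether the effect lasts.

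**Working it through.** **Sample size first.** Conversation is the largest requirement: effect 0.45 SD, baseline correlation 0.5, 90% power, two-sided 5%.

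- n per arm = 2 × (1 − 0.5²) × (1.960 + 1.282)² / 0.45² = 77.8, so 78.
- With 15% dropout: 78 / 0.85 = 91.8, so 92.
- A noncentral-t calculation gives 79, hence 93 per arm (94 with dropout 5/33).

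The stated 95 per arm is reproduced closely. With 0.85 × 95 ≈ 81 per arm observed, power is 91.1% for conversation, 95.6% for word retrieval and 97.5% for COAST. The reduced set is already paid for.

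**Who is outside the six-month analysis.** If the pilot's 15% dropout applies at six months, 0.15 × 285 ≈ 43 participants. At the internal pilot's 65% retention floor, 0.35 × 285 ≈ 100.

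**What a longitudinal model changes at six months.** Simulated trials had 95 per arm, 15% missing at six months, correlation 0.5 with baseline (protocol) and 0.7 between follow-up visits (assumed). They compared the observed-case ANCOVA with one likelihood model for baseline and all follow-up visits:

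| Pattern among those missing at six months | Variance ratio, ANCOVA / longitudinal |
|---|---|
| None return (monotone dropout) | 1.00, identical estimates |
| One third return later | about 1.02 |
| All return later | about 1.05 |

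Six months is the first outcome visit. Only participants who miss it and come back can add anything to the six-month contrast.

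**What it changes at 12 months.** From the protocol: effect 10 and SD 17.38, the latter from an analysis of covariance and so read as the SD after baseline adjustment. Assumed: 81 per arm at six months, six- to 12-month correlation 0.7, about 20% further dropout, and log-odds of dropout rising by 0.7 to 1.0 for each SD lower six-month score, in usual care only.

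To first order, those retained in usual care have a mean six-month score higher by slope × dropout proportion, in SD units. The 12-month contrast shrinks by that shift × 0.7 × 17.38 = shift × 12.17.

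- Slope 0.7: 0.7 × 0.20 = 0.14 SD; 0.14 × 12.17 = 1.7 words; estimate about 8.3.
- Slope 1.0: 1.0 × 0.20 = 0.20 SD; 0.20 × 12.17 = 2.4 words; estimate about 7.6.

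Simulation agrees, with some spread by set-up:

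| Dependence of dropout on six-month score | 12-month ANCOVA, observed cases (true 10) |
|---|---|
| None | 10.0 |
| Usual care only, slope 0.7 | 8.4 to 8.7 (one variant 8.3) |
| Usual care only, slope 1.0 | 7.7 to 8.1 (one variant 7.5) |
| Same slope in both arms | 9.5 to 9.9 |

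The likelihood estimate, which uses the six-month score, stayed at 10.0 to 10.1 in the usual-care-only scenarios. With no informative dropout its 12-month standard error was about 3 to 5% smaller (for example 2.92 against 3.06).

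**Sensitivity to the SD.** If 17.38 were the SD before baseline adjustment, with correlation 0.5 with baseline, the residual correlation is (0.7 − 0.25) / 0.75 = 0.60, the residual SD is 17.38 × √0.75 = 15.05, and the shifts are multiplied by √0.75 = 0.866. The bias is then 0.60 × 15.05 × 0.121 = 1.1 words or 0.60 × 15.05 × 0.173 = 1.6 words, giving estimates of about 8.9 and 8.4.

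**The case against.** The strongest case for the plan is at its primary endpoint. An ANCOVA at the first follow-up visit is valid when missingness depends on baseline and arm. Under monotone dropout the longitudinal model makes the same assumption there and returns the same answer. This stands.

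A reader might infer that a longitudinal model would bring the 43 or so missing participants back into the primary analysis. It would not. Someone with baseline only may be listed in the model but carries no information on the treatment effect.

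The 12-month figures rest on inputs that the protocol does not give. It reports that pilot dropout rose over time, not that it depended on arm or progress, and the bias is small when the dependence is equal in both arms. The nine- and 12-month analyses are also declared exploratory. Both points stand, and they limit the size of the concern.

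The protocol also discloses its restriction right after naming ITT, describes missing data, plans imputation and leaves its detail to an analysis plan that is not shown here. That detail is not missing. But imputation is assigned to a sensitivity analysis, and the trend analysis is not made the source of the visit contrasts. The headline method for the later visits is therefore fixed as observed-case ANCOVA, and that is open to comment.

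**Conclusion.** The concern holds in a limited form. The primary set is mislabelled and its two definitions need reconciling. The separate ANCOVAs at nine and 12 months are a weaker choice than one longitudinal model on data already collected. The possible bias at 12 months is about 1.3 to 2.3 words out of 10 under dropout that depends on the six-month score in usual care only. It is less if 17.38 is not a baseline-adjusted SD, and small if the dependence is the same in both arms. These sizes are illustrations resting on an assumed correlation, dropout rate and dropout slope.

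The documents do not support stronger readings: that the six-month primary estimate is biased, that the trial is underpowered, or that every randomised participant could be made to count. The precision gain is nil to about 5% in variance at six months, and about 3 to 5% in standard error at 12 months.

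**What to change.** 1. Take the nine- and 12-month contrasts from one likelihood-based longitudinal model with baseline, treatment-by-visit terms, an unstructured covariance across visits, and the stratification factors (centre and naming severity). Include everyone with any follow-up. The six-month contrast can come from the same fit. With the same covariates and monotone dropout it is essentially the ANCOVA result, which can be kept as a sensitivity analysis.
2. Describe the six-month set as participants analysed as randomised with an observed outcome (modified ITT), and state the missing-data assumption.
3. Reconcile the two set definitions, saying explicitly how participants seen only at nine or 12 months are handled.

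The cost is wording and modest programming, with no new data and no change to sample size. The downside is reliance on missing at random. For the later visits this is weaker than what the separate ANCOVAs need, because dropout may also depend on earlier observed scores, but it cannot be verified. The planned imputation analysis could be used to probe departures from it.

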#### Randomisation, blinding and allocation concealment

Following baseline assessment, the participant will be randomised to one of the three trial intervention arms. Randomisation will be performed by an online randomisation system developed and maintained through the Sheffield Clinical Trials Research Unit (CTRU). The randomisation sequence will be generated in advance by the trial statistician. Randomisation will be stratified by centre (as heterogeneity between centres is expected), and according to severity of word retrieval at baseline, based on percentage scores on the Naming Objects subtest of the Comprehensive Aphasia Test (severe = 10 to 34%, moderate = 35 to 64%, and mild = 65 to 90%). The research speech and language therapist will then inform the participant which group they have been allocated to and draw their attention to the description of this group in the information sheet.

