#### Data and statistical analysis

##### Sample size

The study aims to recruit 285 participants across 20 speech and language therapy departments (study sites and centres). The sample size of 285 patients in total (95 per arm) is the maximum sample size estimate across the two primary endpoints (word finding ability and functional conversation ability) and key secondary endpoint (patient perception of communication ability) for 90% power and a two-sided significance level of 5%.

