##### Assumptions for the sample size calculation

For improvement in word retrieval the estimated effect size is 10%, with a standard deviation (SD) of 17.38%, from an analysis of covariance (based on results of the pilot study [13]). For assessment of conversation the estimated effect size is 0.45 of a SD (with a correlation between baseline and outcome of 0.5 previously observed in the ACT NoW study). For patient-rated improvement using the COAST questionnaire the estimated effect size is 7.2, with a standard deviation (SD) of 13.5 (with an assumed correlation between baseline and outcome of 0.5). The observed dropout rate was 5 out of 33 (15%; 95% CI: 5 to 32%) in the pilot study, which translated to a completion rate of 28/33 (85%; 95% CI: 68 to 95%) [31].

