Other key issues in designing the protocol arose from the pragmatic nature of the study. First of all, in order to recruit sufficient numbers of participants, at least 20 speech and language departments are required across the United Kingdom. This will allow generalisation of the results to the population of the United Kingdom. However, we expect considerable variation in the usual care provided to people with aphasia in the long term post stroke, with some sites providing impairment based interventions face to face for several months, and others limiting their service provision to hospital care or for a few weeks post-hospital discharge only. The intervention being tested could be implemented in addition to any existing services in practice. The study therefore uses an adjunct design whereby patients continue to receive any ongoing care. This may have the added benefit of recruiting those patients who would not wish to be randomised away from usual care. To account for the heterogeneity expected, the randomisation is to be stratified by site, ensuring representation of different models of usual care in each study group.

There are challenges in involving people with aphasia in research, as they often have difficulty reading or understanding spoken language. The protocol for obtaining informed consent therefore needed careful consideration. In order to adhere to the Mental Capacity Act (2005) in England and the Adults with Incapacity Act (2000) in Scotland, a consent support tool has been included to identify reading and spoken comprehension ability of individuals and recommend the style of information that is likely to best inform each individual. The tool also identifies those participants whose aphasia severity is such that they are unlikely to understand the information sufficiently to provide informed consent and therefore need the involvement of a carer, relative or legal representative. In addition, the reading deficits make completion of standard questionnaire tools such as the EQ-5D difficult and unreliable. We therefore developed and tested an accessible EQ-5D which uses illustrations and visually represented extent of difficulty.

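### The stated ANCOVA omits centre and naming severity, the two factors that stratify the randomisation, so its standard errors are too large wherever those factors predict outcome

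*Protocol article*

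**What the plan says.** **Randomisation.** The section on randomisation, blinding and allocation concealment states: "Randomisation will be stratified by centre (as heterogeneity between centres is expected), and according to severity of word retrieval at baseline". Severity is cut into three bands (10 to 34%, 35 to 64%, 65 to 90%) on the Naming Objects subtest of the Comprehensive Aphasia Test. The Discussion returns to the variation in usual care between departments: "To account for the heterogeneity expected, the randomisation is to be stratified by site".

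**Analysis.** In the Statistical analysis section, after Figure 2, the word-retrieval difference is "adjusted for baseline naming ability, will be analysed using an analysis of covariance (ANCOVA"), and the model is then spelled out: "Terms for treatment and baseline will be fitted into the model". The next outcomes follow suit: "Similar analyses will be undertaken for the endpoints of functional conversation ability" and for COAST, with the nine- and 12-month endpoints handled likewise. Neither centre nor severity band enters any model in the article. That section refers only the imputation details to the statistical analysis plan (SAP); the model terms are fixed in the article itself.

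**The concern.** The article relies on stratification to deal with differences between centres. Stratification does only half of that work. It spreads centres evenly over the arms, so the treatment difference varies less from trial to trial. The ordinary ANCOVA standard error is built from the residual variance. If centre is not in the model, that residual still contains the between-centre variance that the design has removed from the treatment contrast. The reported standard error is then larger than the true one, confidence intervals are too wide, and the test runs below its nominal level.

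The document gives grounds to expect centre effects. Usual care is said to vary considerably by site, and a second therapist at each site makes the follow-up assessments, so centre also carries any assessor effect.

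The severity band matters less evenly. For word retrieval, baseline naming is already a covariate and carries most of the same information. For conversation and COAST, the baseline is presumably that scale's own score, which does not stand in for naming severity.

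The testing sequence makes lost power count more than once, because COAST is reached only after both primary outcomes succeed against both controls.

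**Working it through.** **1. Reproduce the planned sample size.** Inputs from Sample size and Assumptions for the sample size calculation: 90% power, two-sided 5%, conversation effect 0.45 SD, baseline correlation 0.5, dropout 15%. Conversation drives the maximum.

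- n per arm = 2(1.960 + 1.282)² × (1 − 0.5²) / 0.45² = 77.8, so 78 (79 with the t distribution).
- After dropout: 78/0.85 = 91.8, so 92; 79/0.85 = 92.9, so 93. Totals are 276 and 279, against the stated 285 (95 per arm).
- Word retrieval (10 points, SD 17.38 from an ANCOVA) needs 64 per arm, and COAST needs 56, both before dropout.

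The t-based total is within 3% of the plan. No gain from stratification is built into the figure.

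**2. Closed form, perfect balance.** Let ρ be the share of the variance left after baseline adjustment that lies between centres. The documents give no value, so ρ is assumed over a range.

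- Reported SE / true SE = 1/√(1 − ρ).
- Actual two-sided level = 2Φ(−1.96/√(1 − ρ)).
- Conversation, 95 × 0.85 = 80.75 completers per arm: standardised effect 0.45/√0.75 = 0.520; SE √(2/80.75) = 0.157; ratio λ = 3.302.
- Power without centre = Φ((λ − 1.96)/√(1 − ρ)); with centre = Φ(λ/√(1 − ρ) − 1.96).

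| ρ | SE too large by | Actual level | Power without centre | Power with centre |
|---|---|---|---|---|
| 0.01 | 0.5% | 4.9% | 91.1% | 91.3% |
| 0.05 | 2.6% | 4.4% | 91.6% | 92.3% |
| 0.10 | 5.4% | 3.9% | 92.1% | 93.6% |
| 0.15 | 8.5% | 3.4% | 92.7% | 94.8% |
| 0.20 | 11.8% | 2.8% | 93.3% | 95.8% |

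These are upper bounds, because 20 centres × 3 bands give 60 cells with under five patients each (285/60 = 4.75), so balance is incomplete.

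**3. Simulation with imperfect balance.** Setting: 285 patients, 20 centres × 3 severity bands, permuted blocks of 3, 15% dropout, two arms compared, 3,000 trials per setting. The model with treatment and baseline was compared, on the same data sets, with that model plus fixed centre and severity terms. Severity was given an effect beyond baseline, and its correlation with the baseline score was set to 0.8 (close to the word-retrieval case) or 0.3 (closer to conversation and COAST).

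| Severity–baseline correlation | ICC | Type I error without / with | Power without / with |
|---|---|---|---|
| 0.8 | 0 | 5.1% / 5.2% | 90.8% / 90.5% |
| 0.8 | 0.05 | 4.3% / 4.8% | 91.8% / 92.2% |
| 0.8 | 0.10 | 3.7% / 4.7% | 92.1% / 93.0% |
| 0.8 | 0.20 | 3.7% / 5.2% | 92.4% / 95.6% |
| 0.3 | 0 | 4.9% / 4.9% | 91.2% / 91.5% |
| 0.3 | 0.05 | 4.0% / 5.2% | 92.0% / 93.2% |
| 0.3 | 0.10 | 4.2% / 5.2% | 92.1% / 93.6% |
| 0.3 | 0.20 | 3.3% / 5.2% | 93.2% / 96.3% |

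At ICC 0.10 and correlation 0.8, the model without the strata reports a mean SE of 0.157, while the estimates actually vary with an SD of 0.149 to 0.150. The Monte Carlo standard error of a 5% rejection rate is √(0.05 × 0.95/3000) = 0.4 points.

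**4. Effect through the testing sequence.** This is the chance that conversation is significant at 5% against both controls, with 81 completers per arm, balanced centres and correlation 0.5 between the two comparisons from the shared intervention arm. Without against with centre, it is 85.8% vs 87.0% at ICC 0.05, 86.7% vs 89.0% at 0.10, and 88.6% vs 92.7% at 0.20.

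**The case against.** The strongest case is that this is small and errs safely. The treatment estimate is not biased, false positives are not inflated, and power stays above the planned 90% in every scenario. The loss exists only relative to a better model and disappears at ICC 0. The ICC is assumed, and what matters is the ICC left after baseline adjustment, since baseline absorbs part of the case-mix difference between centres. All of this stands. It limits the size but does not remove the mismatch.

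The severity term adds little for word retrieval, where baseline naming is already fitted. That stands too; centre is the factor missing for all three outcomes.

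The Discussion gives the purpose of stratifying by site as having different models of usual care represented in each group, which is achieved whatever model is fitted. That is fair to the stated purpose. The statistical consequence of stratifying on a prognostic factor is the same whatever the motive.

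The full covariate list might be left to the SAP. Silence on covariates in an article would be no finding. Here the article names the terms, extends them to the other outcomes, and refers only imputation to the SAP.

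Finally, the simulation fitted centre as fixed, whereas a random intercept is proposed below. Either removes the mismatch. The choice is secondary.

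**Conclusion.** The point holds. The stated model does not match the stated randomisation, and if centres differ as the authors expect, its standard errors are too large and its tests conservative. For an assumed residual ICC of 0.05 to 0.20, the standard error is overstated by up to 2.6% to 11.8%. Simulated type I error is about 3.3% to 4.3% instead of about 5%. The power loss is about 0 to 3 percentage points per comparison relative to the matching model, and somewhat more (up to about 4 points at ICC 0.20) for success against both controls. There is no loss if centre has no effect.

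These sizes rest on the assumed ICC range, 15% dropout, small blocks within centre-by-severity cells, and the article's conversation assumptions. The planned sample size and its 90% power are not undermined. This should be changed because the mismatch is clear and the correction costs almost nothing, not because validity is at risk.

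**What to change.** Replace the sentence on model terms with: *Terms for treatment, baseline value of the outcome, centre (random intercept) and randomisation severity stratum will be fitted.* Apply the same terms to both primary outcomes, COAST, and the nine- and 12-month analyses, and carry them into the SAP. Fixed centre terms are acceptable if preferred, but one form should be chosen in advance. Settling this before unblinding also avoids a later choice between adjusted and unadjusted results near the 2.5% and 5% thresholds.

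The cost is one sentence in the protocol and SAP. No new data are needed, since centre and severity band are already recorded for randomisation, and no extra participants. If centre turns out not to matter, the fixed-effect version changed simulated power by only about 0.3 points in either direction.

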## Background

Stroke is the largest cause of disability in the United Kingdom with communication impairment affecting one third of survivors [1]. Aphasia is the most common communication impairment acquired post stroke. It is a disorder of language which may affect understanding, expression, reading and writing. Speech and language therapy (SLT) is often received regularly initially but rarely continues after the first few months. Medical instability, fatigue and confusion may reduce full engagement with language therapy in the early weeks post stroke, reducing the opportunity for people to participate in treatment. There is evidence that people can continue to improve their language skills for several years [2]. As the consequences of aphasia remain a problem long term, investigation of interventions to reduce this health burden in the chronic stages post stroke is crucial. The National Stroke Strategy [1] recommends people receive rehabilitation for as long as they benefit from it. Treatment of aphasia that persists beyond the first few months post stroke is often not available through NHS services in the United Kingdom as ongoing therapy is costly through face-to-face SLT and places greater demands on limited resources.

Meta-analysis in a Cochrane review [2] of SLT for aphasia following stroke suggests some effectiveness of aphasia therapy [2]. Adequately powered randomized controlled trials (RCTs) in this field are rare except for recent studies of SLT intervention in the first few weeks post stroke. Laska *et al*. [3] randomised 123 patients with aphasia to receive 45 minutes of SLT a day for 21 days, starting within two days of stroke onset, or no SLT intervention. Severity of the aphasia was not reduced. A recently completed study, ACT NoW [4], randomised 170 people in hospital post stroke to SLT intervention or attention control (informal conversation with paid visitors) for up to four months. No significant differences between groups were shown and the authors suggested that the intervention may have been provided too early in the stroke pathway. As aphasia persists for many stroke survivors, therapy in the longer term also warrants investigation using adequately powered RCTs. Although rapid spontaneous recovery may occur in the first few months, there is preliminary evidence to suggest targeted and intensive SLT treatments can promote further improvement in the latter months [5-7].

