### Inclusion criteria

Participants will be included if they meet the following criteria:Aged 18 or over;Diagnosis of stroke(s);Onset of stroke at least four months prior to randomisation;Diagnosis of aphasia, subsequent to stroke, as confirmed by a trained speech and language therapist;Ability to retrieve 10 to 90% of words on the Comprehensive Aphasia Test Naming Objects subtest (score of 5 to 43 out of 48);Ability to perform a simple matching task in StepByStep with at least 50% accuracy (to confirm sufficient vision and cognitive ability) andAbility to repeat at least 50% of words in a simple word repetition task in the StepByStep© program.

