### Baseline assessment

Initial assessment will be performed by the local research speech and language therapist once informed consent has been given. This will include collection of the following demographic data: aphasia type, age, gender, time post-onset of stroke and type and location of stroke (if known). Baseline information will also include results of the standardised naming test - Naming Objects subtest of the Comprehensive Aphasia Test (performed as part of eligibility testing during screening) and the Comprehension of Spoken Sentences subtest of the CAT to provide information on the comprehension ability of the participants [24]. Baseline measures relating to the study outcomes are summarised in Table 1.

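### The primary ANCOVA adjusts for baseline score only; pre-specifying time since stroke, which is already collected, would give a modest gain in precision at almost no cost

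*Protocol article*

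**What the plan says.** All references are to the protocol article.

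- **Model (Statistical analysis, text after Figure 2).** For word finding the ANCOVA is fixed as "Terms for treatment and baseline will be fitted into the model". The other endpoints follow: "Similar analyses will be undertaken for the endpoints of functional conversation ability", and likewise for COAST. In this part of the text only the imputation details are expressly left to the SAP.
- **Eligibility (Inclusion criteria).** "Onset of stroke at least four months prior to randomisation". No upper limit is given.
- **Data collected (Baseline assessment).** Time since stroke is among the demographic items recorded before randomisation: "aphasia type, age, gender, time post-onset of stroke and type and location of stroke (if known".
- **Allocation (Randomisation, blinding and allocation concealment).** "Randomisation will be stratified by centre (as heterogeneity between centres is expected), and according to severity of word retrieval at baseline". Time since stroke is not a factor.
- **Sample size.** "The sample size of 285 patients in total (95 per arm) is the maximum sample size estimate across the two primary endpoints" and the key secondary endpoint, with 90% power at a two-sided 5% level.

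**The concern.** Both primary outcomes are changes over six months. The Background says "Although rapid spontaneous recovery may occur in the first few months", that people can go on improving for several years, and that therapy is usually regular early on and rare later. With a four-month minimum and no maximum, the sample can mix people close to the early recovery phase, some perhaps still in therapy, with people many years after stroke. Two people with the same baseline naming score at four months and at four years may have different expected change. The baseline score and the severity band record where a person starts, not how fast that person is still changing, so they may not stand in for time since stroke.

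If time since stroke predicts the six-month outcome given baseline, the stated model leaves explainable variance in the residual. It also gives no pre-specified way to adjust if the arms differ on it by chance. Adding the covariate after the data are seen would be open to challenge, and the article's allowance for alternative analyses concerns violated model assumptions, not imbalance.

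**Working it through.** **Inputs from the article (Sample size and its assumptions).** Conversation: effect 0.45 SD, baseline–outcome correlation 0.5. Words: effect 10, SD 17.38, the SD already from an ANCOVA. COAST: effect 7.2, SD 13.5, assumed correlation 0.5. Two-sided 5%, 90% power, 95 per arm, 15% dropout (5/33).

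**1. Reproduce the stated sample size.** Conversation drives the maximum. The residual SD after baseline adjustment is √(1 − 0.5²) = 0.866.

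- Normal approximation: n = 2(1.960 + 1.282)² × 0.75 / 0.45² = 77.8, so 78 per arm; 78/0.85 gives 92.
- t-based: 79 per arm; 79/0.85 gives 93, and 79/(28/33) gives 94.

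This is within two of the stated 95. Words need 76 per arm and COAST 66 after dropout (normal approximation). The planned sample size therefore follows from baseline adjustment alone.

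**2. Power if time since stroke is added.** The article gives no association between time since stroke and outcome. Assume a partial correlation r of log time since stroke with the six-month outcome, given baseline, of 0.1 to 0.4. The residual SD is multiplied by √(1 − r²). For conversation the standardised effect is 0.45 / (0.866 √(1 − r²)). Completers per arm: 95 × 0.85 = 80.75. The equivalent number of extra participants is 285/(1 − r²) − 285. Power is t-based.

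| r | r² | Conversation power | Words power | Equivalent extra participants |
|---|---|---|---|---|
| 0 | 0 | 90.7% | 95.3% | 0 |
| 0.1 | 0.01 | 91.0% | 95.5% | 3 |
| 0.2 | 0.04 | 91.8% | 96.0% | 12 |
| 0.3 | 0.09 | 93.1% | 96.8% | 28 |
| 0.4 | 0.16 | 94.7% | 97.8% | 54 |

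The normal approximation gives 91.0% for conversation and 95.5% for words at r = 0, so the choice of method shifts the level by a few tenths of a point.

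**3. Validity when it is left out.** Two-arm trials were simulated with 81 per arm, baseline correlation 0.5, a skewed distribution of time since stroke, and r² of 0.05, 0.10 and 0.15 (10,000 runs each). With the covariate omitted, type I error was 4.7% to 5.1% and the mean error of the estimate was at most 0.003 SD.

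**4. Chance imbalance.** With 81 per arm, the SD of the difference in mean log time since stroke is √(2/81) = 0.157 SD. Because r is conditional on baseline, the shift in outcome SDs also carries the factor 0.866. At r = 0.3:

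- One-SD imbalance: 0.157 × 0.3 × 0.866 = 0.041 outcome SD; 0.041/0.45 = 9% of the planned effect.
- Imbalance at its 95% limit: 1.96 × 0.157 = 0.308 SD; 0.308 × 0.3 × 0.866 = 0.080 outcome SD; 0.080/0.45 = 18%.

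For comparison, the standard error of the baseline-adjusted difference is about 0.866 × 0.157 = 0.136 outcome SD, so a one-SD imbalance at r = 0.3 moves the estimate by 0.3 standard errors.

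**The case against.** The best case for the plan is that an ANCOVA on treatment and baseline is a sound analysis, contradicts nothing else in the article and matches the sample size calculation. Further covariates and adjusted sensitivity analyses are often set out in the SAP, which is not at hand and may already include this one. Much of this stands and limits the point to a recommendation. It does not remove the point, because the article states the model terms rather than deferring them, and the variable is already collected.

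Three stronger inferences are tempting, and the documents do not support them:

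- **That randomisation leaves time since stroke unbalanced.** It is balanced in expectation; it is only not stratified. Chance imbalance is already reflected in the standard error, and step 3 shows no bias over randomisations and no inflation of type I error.
- **That the article shows time since stroke to be prognostic in this sample.** It places rapid recovery in the first few months. The four-month minimum and the requirement for persistent aphasia probably exclude much of that period. A remaining gradient after four months is plausible but is an inference, and r may be near 0.1 or lower.
- **That the trial is underpowered without it.** Power is already above 90% for conversation and about 95% for words.

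It can also be said that the same sentence omits centre and naming severity, which were chosen for stratification (centre because heterogeneity was expected), and that these have a firmer claim to a place in the model. That is fair. It is a neighbouring point that the same edit could address.

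**Conclusion.** The point holds as a minor one about precision and pre-specification. The stated model omits a baseline variable that is recorded, has no upper limit at entry, is not stratified on, and is linked by the article to the pace of recovery. The consequence is some lost precision on both primary outcomes and on COAST, and no planned adjustment for chance imbalance. Unbiasedness, type I error and the sample size justification are not in question.

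The size depends wholly on an assumed r. For conversation the gain is about 0.3 points of power at r = 0.1, 1.1 at 0.2, 2.4 at 0.3 and about 4 at 0.4; for words it is smaller. The figures also assume 15% dropout and the article's baseline correlation of 0.5. The equivalent of 28 extra participants applies only at r = 0.3 and should not be read as an estimate for this trial.

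**What to change.** In the Statistical analysis section, add log(time since stroke at randomisation) as a pre-specified continuous covariate beside the baseline score in the ANCOVA for words, TOMS and COAST. The log scale suits a variable with a minimum and a long right tail. If the team prefers to keep the present primary model, the minimum is a pre-specified sensitivity analysis with this covariate. Either should be fixed before unblinded data are seen.

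The cost is one line of text and one degree of freedom per model, with no new data and no change to the sample size or the testing sequence. The drawback is that the gain may be negligible if time since stroke is only weakly prognostic after four months.
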